### **8.11 Follow up of subjects withdrawn from treatment**

Should a subject request or decide to withdraw from the study, all efforts will be made to complete and report the observations as thoroughly as possible up to the date of withdrawal, and for subjects who are withdrawn, the follow-up assessments should be performed within 8-10 days after the last drug administration.

### **8.12 Study Termination**

The sponsor, investigator or Institutional Review Board (IRB)/Independent Ethics Committee (IEC) may terminate the study at any time if any of the following criteria are met.

- There is new information about the study drug that indicates the risk/benefit profile is no longer acceptable for the study to continue.
- There is a significant deviation from the protocol or violation of Good Clinical Practice (GCP) that compromises the study results, subject safety or ability to address the study objectives.

If a trial is prematurely terminated or suspended for any reason, the investigator should promptly inform the trial subjects and should assure appropriate therapy and follow-up. The sponsor, IRB/IEC and regulatory authority (ies) should be notified

## **9. SAFETY REPORTING**

### **9.1 Safety and tolerability assessments and reporting**

#### **9.1.1 Safety Monitoring**

In this study with small sample size and short duration, the independent physician will perform safety control by reviewing clinical safety parameters throughout the conduct of the study. Clinical safety parameters will include laboratory analysis, urine analysis and ECG

#### **9.1.2 Section 10 WMO event**

In accordance to section 10, subsection 1, of the WMO, the investigator will inform the subjects and the reviewing accredited IEC if anything occurs, on the basis of

---

which it appears that the disadvantages of participation may be significantly greater than was foreseen in the research proposal. The study will be suspended pending further review by the accredited IEC, except insofar as suspension would jeopardise the subjects' health. The investigator will take care that all subjects are kept informed.

### **9.1.3      *Adverse events and serious adverse events***

Adverse events are defined as any undesirable experience occurring to a subject during a clinical trial, whether or not considered related to the investigational drug. All adverse events reported spontaneously by the subject or observed by the investigator or his staff will be recorded. A serious adverse event is any untoward medical occurrence or effect that at any dose

1. results in death;
2. is life threatening (at the time of the event);
3. requires hospitalisation or prolongation of existing inpatients' hospitalisation;
4. results in persistent or significant disability or incapacity;
5. is a congenital anomaly or birth defect;
6. is a new event of the trial likely to affect the safety of the subjects, such as an unexpected outcome of an adverse reaction, lack of efficacy of an IMP used for the treatment of a life threatening disease, major safety finding from a newly completed animal study, etc.

All SAEs will be reported to the accredited IEC that approved the protocol, according to the requirements of that IEC.

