### *Toxicology*

TRC150094 was found to be non-mutagenic in AMES test, Mouse lymphoma assay and Micronucleus test. TRC150094 was found to be well tolerated in acute studies in rats and mice by clinical and parenteral route. Chronic repeat dose toxicity studies were conducted in Wistar rats (26 week) and Beagle dogs (39 week). There were no test item related clinical signs observed in rat and dog treated chronically. However, Beagle dogs treated in 4 week study showed emesis at 2-4 hr post dosing at high dose of 450 mg/kg/day. Transient reduction in thyroid hormones (total and free T4) was observed in rat studies at top doses of 180 and 360 mg/kg/day, while in dog it was seen in 4 week study at top dose of 450 mg/kg/day. Thyroid hormone profile remained unaltered in 39 week dog toxicity study up to a high dose of 75 mg/kg/day. The change in thyroid hormone profile is considered as test item related pharmacological effect. Repeated exposure of TRC150094 revealed kidney as target organ for toxicity in both rat and dog species. Increased kidney weight was evident at highest doses up to the chronic duration in rats. Microscopically, dilated renal tubules and nephropathy was seen at highest doses of 180 and 360 mg/kg/day in rats. Beagle dogs treated in 4 week study at 450 mg/kg/day revealed dilated renal tubules, lymphocytic infiltration and nephropathy in kidney and degeneration of seminiferous

tubules of testes. There were no such alterations observed in dog treated at high dose of 75 mg/kg/day in 13 and 39 week studies. No observed adverse effect level (NOAEL) doses in Wistar rat and Beagle dog is 60 and 75 mg/kg/day, respectively in chronic toxicity studies which demonstrated very high safety margins. TRC150094 did not have any adverse impact on male and female fertility indices studied in rats and found to be non-teratogenic in rat and rabbits.

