#### **8.2.2 *Breaking the randomisation code***

The investigator will have access to one set of sealed code-break envelopes. In the event of an emergency, e.g. a serious adverse event (SAE), the investigator may open the subject's envelope to determine the study drug administered to the subject. If

---

possible, the sponsor should be notified before the blind is broken; otherwise, the sponsor will be notified as soon as possible. In addition the IEC (Independent Ethics Committee) will also be notified if the code is broken during the study. The date, time and reason, and the name of the person who opened the envelope, will be recorded in the subject's CRF and on the individual envelope. If the blind is broken, the subject must be withdrawn from the study and replaced.

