### **9.1.4      *Reporting of adverse event***

For each subject, all AEs will be collected from the time of first dose administration through to the post-study follow-up visit. On arrival at the trial unit, at regular intervals during study, and at follow up, each subject will be asked a non-leading question such as "How have you been feeling since last asked?" Any AEs reported in response to questioning, as well as AEs reported spontaneously and occurring at any other time after dosing, will be recorded in the subject's CRF. For each AE, the following information will be recorded:

- AE description
- start and stop dates and times

- 
- single episode or intermittent
  - severity: mild (easily tolerated), moderate (interferes with daily activities) or
  - severe (prevents normal daily activities)
  - relationship to study drug (definite, probable, possible, unlikely or not related)\*
  - outcome (resolved, resolved with sequelae, or ongoing)
  - whether serious or not.

\* Definitions for the relationship to study drug assessment, to be made by the investigator, are as follows:

**Definite:** The AE follows a reasonable temporal sequence from administration of the drug, abates on withdrawal of study drug and re-appears upon re-administration (rechallenge).

**Probable:** The AE follows a reasonable temporal sequence from the administration of the drug, abates on withdrawal of study drug and cannot be reasonably explained by the known characteristics of the subject's clinical state or other factors, such as concomitant medication.

**Possible:** The AE follows a reasonable temporal sequence from the administration of the drug but could have been produced by the subject's clinical state or other factors, such as study procedures or concomitant medication.

**Unlikely:** The temporal association between the AE and the drug is such that the drug is unlikely to have any reasonable association with the AE.

**Not related:** The AE does not follow a reasonable temporal sequence from the administration of the drug or the AE can be reasonably explained by other factors, such as concomitant medication.

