### **9.1.5 Procedures for reporting SAEs**

All SAEs should be reported immediately to the sponsor. The immediate reports should be followed promptly by detailed, written reports. The immediate and follow-up reports should identify a subject by his initials and the subject number, and not by personal information such as name or address. The investigator should also comply

---

with the applicable regulatory requirement(s) related to the reporting of unexpected serious adverse drug reactions to the regulatory authority(ies) and the IRB/IEC.

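### SAE criterion 6 mixes subject events with programme information, and no criterion clearly covers an expected but medically important event below life-threatening, disabling or hospitalised

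*Protocol*

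**What the plan says.** Section 9.1.3 of the protocol starts at subject level: "Adverse events are defined as any undesirable experience occurring to a subject during a clinical trial". It then lists six criteria, any one of which makes an event serious. The first five are death, threat to life, admission or its prolongation, lasting or significant disability, and congenital anomaly. The sixth applies if something "is a new event of the trial likely to affect the safety of the subjects, such as an unexpected outcome of an adverse reaction". Its further examples are lack of efficacy of a product used in a life-threatening disease and a "major safety finding from a newly completed animal study, etc".

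Seriousness then decides what happens next:

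- Section 9.1.5: "All SAEs should be reported immediately to the sponsor". The reports are to identify the subject by initials and subject number.
- Section 9.1.3: all SAEs go to the ethics committee.
- Sections 9.1.7, 9.1.8 and 12.3: SUSAR handling and the annual reports are built on serious events or reactions.
- Section 10.4: frequency tables show seriousness, and rates are subjects with at least one AE out of subjects treated.

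For an AE that is not serious, section 9.1.4 asks for recording in the CRF and sets no time limit. Its outcome field reads "outcome (resolved, resolved with sequelae, or ongoing", with no further value.

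**The concern.** A definition of seriousness has to do two jobs. It must pick out events in individual subjects, and it must let the investigator escalate an event that matters medically even when no listed outcome has occurred. The sixth criterion does the first job only in part and the second not clearly at all.

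The events left in doubt are ones that the protocol itself foresees. The Synopsis (Benefit and risk) and section 11.3 name hypoglycaemia as a risk of the clamp. The Toxicology part of section 7.2.2 states: "Repeated exposure of TRC150094 revealed kidney as target organ for toxicity in both rat and dog species".

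At stake is how fast the sponsor and the ethics committee hear of such an event, and whether two centres classify the same event alike. Safety is part of the primary objective (section 4.1), and section 10.4 plans no significance testing on it. The safety conclusion therefore rests on descriptive classification.

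**Working it through.** The protocol gives no figure on this point and no calculation applies. The check sets the criteria beside the sections that use them.

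**Step 1. Are criterion 6's examples events in a subject?**

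| Example | Experience of a subject (9.1.3)? | Reportable by subject number (9.1.5)? | Countable per subject (10.4)? |
|---|---|---|---|
| Unexpected outcome of an adverse reaction | Yes | Yes | Yes |
| Lack of efficacy in a life-threatening disease | Cannot arise: the trial studies men with increased cardiometabolic risk | No | No |
| Animal-study finding | No | No | No |

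One example of three fits the definition that opens the same section.

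**Step 2. Which events can be serious without admission?** Death, disability and an event that "is life threatening (at the time of the event") all qualify without a hospital stay. The gap is therefore limited to important events below those thresholds.

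**Step 3. Test two foreseen events.**

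- *Clamp hypoglycaemia corrected in the unit.* Section 8.4.1 has glucose checked every 10 minutes with a variable glucose infusion running, so correction on site without admission is plausible. If the episode is not life threatening, criteria 1 to 5 are not met. Because hypoglycaemia is a named risk, it is neither clearly new nor an unexpected outcome, so criterion 6 is not clearly met.
- *Marked creatinine rise managed as an outpatient.* Criteria 1 to 5 are not met. Criterion 6 is met only on a generous reading, as an unexpected outcome of a reaction.

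**Step 4. Follow the classification.** An investigator who applies the list as printed can record either event as a non-serious AE. Section 9.1.5 then does not apply, and neither does the ethics committee clause in 9.1.3. The remaining requirement is the CRF entry under 9.1.4.

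**Step 5. Exposure, without a rate.** With 40 subjects and two clamps each, there are 40 × 2 = 80 clamp sessions. Of these, 40 are on Day 28. The 40 on Day 0 precede the first dose on Day 1, while 9.1.4 collects AEs only from the first dose. Yet section 8.5 and Appendix B schedule an AE check on Day 0. For Day 0, then, even whether an event is collected as an AE is unsettled.

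**Step 6. Outcome codes against criterion 1.** Death is the first SAE criterion. None of the three outcome values in 9.1.4 describes it.

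**The case against.** Several objections stand and limit the point.

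- Criteria 2 and 4 need no admission, so it would be wrong to say that nothing short of hospitalisation can be serious.
- Criterion 6 is not only programme news. Its first example is at subject level and its list is open-ended, so a generous investigator could include some of the events in question. A rule that depends on generosity, however, can be applied differently at two centres.
- Under 9.1.1 an independent physician reviews laboratory, urine and ECG data throughout, which would include creatinine. Under 9.1.2 the ethics committee is informed if the disadvantages appear significantly greater than foreseen. Section 9.1.9 follows all AEs until they abate or stabilise, and section 12.1 has the sponsor inspect eCRFs at regular intervals. These soften the consequence, but none makes an individual event serious or immediately reportable.
- The kidney signal is nonclinical, with microscopic changes at the highest doses, and section 7.2.3 reports no clinically relevant drug-related change in renal markers in the first multiple-dose cohort. This bears on how likely a renal event is, not on how it would be classified.

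Two stronger readings are tempting, and the protocol does not support them.

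- A reader might infer that an animal finding, being nominally an SAE, would license opening code envelopes. Section 8.2.2 says "In the event of an emergency, e.g. a serious adverse event (SAE), the investigator may open the" envelope of the subject concerned. The condition is an emergency and an SAE is one example of it. An animal finding is not an emergency in a subject, and a non-serious emergency already permits opening.
- A reader might infer that important events would vanish from the report. Section 10.4 also tabulates severity and drug relation, and gives laboratory shift tables and QTc summaries. The events would be reported, but not as serious.

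It can also be said that outcome coding belongs to the Data Management Plan. That is fair for most codes, but section 9.1.4 prints a list that omits the outcome named first in 9.1.3.

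**Conclusion.** The point holds in a limited form. Criterion 6 is internally inconsistent: two of its three examples conflict with the AE definition, the subject identifiers and the per-subject counts elsewhere in the protocol. The six criteria also leave no clear place for an expected or procedure-related event that is medically important in one subject but below life-threatening, disabling or hospitalised. In such a case the sponsor's notice changes from immediate to no stated time.

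No numerical effect on SAE rates can be given. The protocol states no frequency for these events beyond calling clamp hypoglycaemia very rare, and any count would be an assumption. The conclusion rests on investigators applying the printed criteria as written and on there being no event-of-special-interest list elsewhere in the protocol; none was found. The change is worth making because the affected events are foreseen risks and the repair is short.

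**What to change.** 1. In 9.1.3, replace criterion 6 with a subject-level one, for example: *is another medically important event in a subject that, in the investigator's judgement, may jeopardise that subject or may need intervention to prevent one of outcomes 1 to 5.*
2. Move the programme-level text (animal findings, lack of efficacy in a life-threatening disease) to 9.1.2 or 9.1.7 as new safety information to be notified, stating that it is not an SAE.
3. In 9.1.4, add a fatal value to the outcome list.
4. Reconcile the start of AE collection in 9.1.4 with the Day 0 AE check in 8.5 and Appendix B. Otherwise the new criterion may not reach events at the Day 0 clamp.

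The change affects reporting and classification only, not clinical management. It costs a few lines of protocol text, one eCRF code and possibly a small number of additional SAE reports.

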### **9.1.4      *Reporting of adverse event***

For each subject, all AEs will be collected from the time of first dose administration through to the post-study follow-up visit. On arrival at the trial unit, at regular intervals during study, and at follow up, each subject will be asked a non-leading question such as "How have you been feeling since last asked?" Any AEs reported in response to questioning, as well as AEs reported spontaneously and occurring at any other time after dosing, will be recorded in the subject's CRF. For each AE, the following information will be recorded:

- AE description
- start and stop dates and times

- 
- single episode or intermittent
  - severity: mild (easily tolerated), moderate (interferes with daily activities) or
  - severe (prevents normal daily activities)
  - relationship to study drug (definite, probable, possible, unlikely or not related)\*
  - outcome (resolved, resolved with sequelae, or ongoing)
  - whether serious or not.

\* Definitions for the relationship to study drug assessment, to be made by the investigator, are as follows:

**Definite:** The AE follows a reasonable temporal sequence from administration of the drug, abates on withdrawal of study drug and re-appears upon re-administration (rechallenge).

**Probable:** The AE follows a reasonable temporal sequence from the administration of the drug, abates on withdrawal of study drug and cannot be reasonably explained by the known characteristics of the subject's clinical state or other factors, such as concomitant medication.

**Possible:** The AE follows a reasonable temporal sequence from the administration of the drug but could have been produced by the subject's clinical state or other factors, such as study procedures or concomitant medication.

**Unlikely:** The temporal association between the AE and the drug is such that the drug is unlikely to have any reasonable association with the AE.

**Not related:** The AE does not follow a reasonable temporal sequence from the administration of the drug or the AE can be reasonably explained by other factors, such as concomitant medication.

### **9.1.5 Procedures for reporting SAEs**

All SAEs should be reported immediately to the sponsor. The immediate reports should be followed promptly by detailed, written reports. The immediate and follow-up reports should identify a subject by his initials and the subject number, and not by personal information such as name or address. The investigator should also comply

---

with the applicable regulatory requirement(s) related to the reporting of unexpected serious adverse drug reactions to the regulatory authority(ies) and the IRB/IEC.

#### **9.1.6      *Emergency procedures***

The subject should be given supportive treatment depending on the symptoms.

#### **9.1.7      *Suspected unexpected serious adverse reactions (SUSAR)***

Adverse reactions are all untoward and unintended responses to an investigational product related to any dose administered. Unexpected adverse reactions are adverse reactions, of which the nature, or severity, is not consistent with the applicable product information (e.g. Investigator's Brochure for an unapproved IMP or Summary of Product Characteristics (SPC) for an authorised medicinal product). The sponsor will report expedited the following SUSARs to the IEC: SUSARs that have arisen in the clinical trial that was assessed by the IEC; SUSARs that have arisen in other clinical trial of the same sponsor and with the same medicinal product, and that could have consequences for the safety of the subjects involved in the clinical trial that was assessed by the IEC. The remaining SUSARs will be recorded in an overview list (line-listing) that will be submitted once every half year to the IEC. This line-listing provides an overview of all SUSARs from the study medicine, accompanied by a brief report highlighting the main points of concern. The sponsor will report expedited all SUSARs to the competent authority, the Medicine Evaluation Board and the competent authorities in other Member States. The expedited reporting will occur not later than 15 days after the sponsor has first knowledge of the adverse reactions. For fatal or life threatening cases the term will be maximal 7 days for a preliminary report with another 8 days for completion of the report.

#### **9.1.8      *Annual safety report***

In addition to the expedited reporting of SUSARs, the sponsor will submit, once a year throughout the clinical trial, a safety report to the accredited IEC's, competent authority, Medicine Evaluation Board and competent authorities of the concerned Member States. This safety report consists of:

- a list of all suspected (unexpected or expected) serious adverse reactions, along with an aggregated summary table of all reported serious adverse reactions, ordered by organ system, per study;

- 
- a report concerning the safety of the subjects, consisting of a complete safety analysis and an evaluation of the balance between the efficacy and the harmfulness of the medicine under investigation.

#### **9.1.9      *Follow-up of adverse events***

All adverse events will be followed until they have abated, or until a stable situation has been reached. Depending on the event, follow up may require additional tests or medical procedures as indicated, and/or referral to the general physician or a medical specialist.

## **10. DATA MANAGEMENT AND STATISTICAL ANALYSIS**

### **10.1 Sample Size Calculation**

It is intended that 40 subjects (20 subjects in India and other 20 in Amsterdam, Netherlands) will complete the study. No formal sample size calculation has been performed. We calculated that a sample size of 20 in each group will have 80% power to detect an absolute difference in Rd of at least 15  $\mu\text{mol/kg}\cdot\text{min}$  (measure for peripheral insulin sensitivity), before and after treatment, using a Wilcoxon (Mann-Whitney) rank-sum test with a 0.05 two-sided significance level and assuming that the common standard deviation is 15.

### **10.2 Data Handling**

Data obtained in this study will be collected in eCRF prepared by the CRU of the Academic Medical Centre, Amsterdam. The eCRF will be completed and monitored in accordance with the principles of GCP. Source data is defined as all information in original records and certified copies of original records of clinical findings, observations, or other activities in a clinical trial necessary for the reconstruction and evaluation of the trial. Source documents are original documents, data and records, such as laboratory printouts, 12-lead ECG reports, dispensing records, and subject files. Data recorded directly into the eCRFs will be considered as source. Full details of procedures for data handling will be documented in the Data Management Plan. AEs, medical history, and pre-existing (concurrent) conditions will be coded using the Medical Dictionary for Regulatory Activities (MedDRA). Drugs will be coded using the World Health Organization (WHO) Drug Dictionary.

